#### Eligibility criteria

Potentially eligible patients will be identified and recruited by respiratory nurses during out-patient COPD control visits. The nurses determine eligibility according to the inclusion and exclusion criteria listed below:

#### Inclusion criteria

Age 18 years or olderClinical diagnosis of COPD defined as the ratio of forced expiratory volume at 1 s (FEV1) to forced vital capacity (FVC) < 0.70 and no history of asthmaFEV1 < 50%, corresponding to severe or very severe airflow limitationSymptoms equivalent to the Medical Research Council dyspnea scale (MRC) from 2 to 5

#### Exclusion criteria

Participation in/or recent completion of pulmonary rehabilitation within the last 6 months before start of interventionDementia/ Cognitive impairment or symptomatic psychiatric illnessAn impaired hearing and / or vision disability which means that the instructions are not understoodUnable to understand and speak DanishUnable to read DanishSevere co-morbidity which means that exercise is contraindicated

Eligible patients receive written information of the study by the respiratory nurses and verbal information about the study is given by the investigator or project staff. The investigator ensures that all questions regarding participation are answered before the patient is asked to participate in the study. According to the ethical guidelines for medical research in Denmark, all patients are encouraged to consider consent for at least 24-h before making the decision. Patients who agree to participate will be asked to sign an informed consent form to be included in the study. The patient will keep the original document and a copy will be archived with the Case Report Form (CRF).

### Blinding

To ensure concealment of allocation a senior manager from another research department with no interest in the project, will provide the draw and will be responsible for the randomization list, which will not be available to the investigator. The senior manager will inform the investigator about the allocation, and the investigator or the project staff will subsequently inform the patient about the allocation and when to begin CORe or CCRe.

All assessors are blinded to group allocation and previous test results. Due to the nature of the study the patients cannot be blinded, but prior to the assessments they are reminded not to disclose their group allocation to the assessors. In case of failure keeping the outcome assessor blinded (that is, if a participant reveals his/her allocation) a second assessor will be available to step in and conduct the assessment on another day.

To avoid experimenter’s (subconscious) bias the biostatistician who perform the data analyses and validate the results will be blinded to group allocation. The research group will interpret the results, and the conclusion will be prepared in two versions before the allocation code is broken (one assuming that arm A is the intervention, and one assuming that arm B is the intervention).

### Sample size

For the study’s primary endpoint, the 6-min walk test (6MWT) which assesses distance (in meters, 6MWD) walked over 6 min, a change of 26 m is considered to be a minimal clinically relevant difference (MIREDIF) in patients with severe and very severe COPD [26, 27]. Based on a two-sample independent t-test with the given MIREDIF of 26 m, standard deviation of 44.6 m based on data published by Puhan et al. 2011 [27], power of 80% and significance level of 0.05 47 patients will be needed in each group, 94 in total. A dropout rate of 30% is assumed, resulting in 134 patients being included in the final study population.

#### Power estimations for secondary outcomes

We performed power estimations for all secondary outcomes based on the decided inclusion of 134 (67 in each group) patients, and expected standard deviation (SD) and an existing minimal clinical important difference (MCID) for each outcome (Table 2). The decided sample size makes it possible to detect clinically relevant differences in secondary outcomes for respectively; muscle strength and leg endurance, symptoms, anxiety and depression, and health-related quality of life (HRQOL) all corresponding with a power above 80% to reject the null hypothesis (type I error 5%). The outcomes for disease specific quality of life and physical activity were both have a power below 80%, and must be considered as exploratory outcomes (Table 2).

**Table 2 Tab2:** Anticipated power on secondary outcomes

Variables	Instrument	Subscales	Cronbach’s alpha	Hypothesized Difference/ SD (anticipated power)
Muscle strength and endurance legs	30 s sit-to-stand test	Total numbers of repetitions	NR (not reported)	2.0/2.5 (0.99)
Symptoms	COPD Assessment Test (CAT)	Eight symptom questions (0–5 points) Total score 0–40 points	0.88	3.0/5.5 (0.88)
Disease specific quality of life	Clinical COPD Questionnaire (CCQ)	Ten items, three domain score (symptoms, functional and mental) and overall score. Items score ranges from 0 to 6	Overall score 0.91 Symptom score 0.78 Functional score 0.89 Mental score 0.80	Overall score 0.4/1.1 (0.55)
Anxiety and depression	Hospital Anxiety and Depressions Scale (HADS)	HADS-A scale (0–21) HADS-D scale (0–21)	HADS-A 0.83 HADS-D 0.82	HADS-A 1.5/2.5 (0.93) HADS-D 1.5/2.5 (0.93)
Health-Related Quality of Life	EuroQol 5-Dimension Questionnaire (EQ-5D)	EQ5D-questionnaire (mobility, self-care, usual activities, pain/discomfort, and anxiety/depression) Norm based utility score (−0.624–1.000) EQ5D-VAS (0–100 mm)	Not relevant – only one question in each dimension	EQ5D-VAS 8/16 (0.82)
Physical activity	*active*PAL™ activity monitor (PAL Technologies Ltd., Glasgow, UK)	Steps per day Minutes lying/sitting Minutes standing/walking Number of body transitions per day	NR (not reported)	Steps per day 1100/2262 (0.50)

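### Table 2 computes secondary-outcome power without the 30% dropout that the plan assumes, so CAT and EQ-VAS do not have the claimed power above 80%

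*Protocol article*

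**What the plan says.** The Sample size section derives the primary requirement from a t-test: "Based on a two-sample independent t-test with the given MIREDIF of 26 m, standard deviation of 44.6 m", with 80% power and "significance level of 0.05 47 patients will be needed in each group, 94 in total". It then inflates: "A dropout rate of 30% is assumed, resulting in 134 patients being included in the final study population". On these figures 134 is the number randomized, and about 94 are expected to provide the outcome.

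The following section, Power estimations for secondary outcomes, starts from a different number: "We performed power estimations for all secondary outcomes based on the decided inclusion of 134 (67 in each group) patients". Table 2 gives the anticipated powers: sit-to-stand 0.99, CAT 0.88, CCQ 0.55, HADS-A and HADS-D 0.93, EQ-VAS 0.82, steps per day 0.50. The text describes muscle strength and endurance, symptoms, anxiety and depression, and health-related quality of life as "all corresponding with a power above 80% to reject the null hypothesis". Disease-specific quality of life (CCQ) and physical activity fall below that line and "must be considered as exploratory outcomes".

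Elsewhere, Table 1 and the section Secondary outcome measures list CCQ as secondary. Table 1 and the activity-monitor paragraph call physical activity exploratory. The abstract lists both disease-specific quality of life and physical activity as secondary.

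**The concern.** Two adjacent paragraphs use different evaluable numbers for the same trial. Table 1 schedules the walk test, sit-to-stand, CAT, CCQ, HADS and EQ-5D at the same 10/12-week visit. A patient lost to the primary outcome is therefore also lost to the others, and nothing in the article suggests that the questionnaires would be more complete.

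Two things are at stake. First, a non-significant CAT or EQ-VAS result would be read as coming from a comparison with more than 80% power to detect a clinically relevant difference, when the design does not provide that. Second, the section sorts outcomes by the 80% line, so an optimistic N decides which outcomes are called exploratory.

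**Working it through.** **Inputs.** Differences, SDs and stated powers come from Table 2. The dropout rate (30%) and the 47 per arm come from Sample size. The 1:1 allocation comes from Randomization. The activity monitor is worn by the first 68 patients only (24-h physical activity paragraph), that is 34 per arm. Alpha is 0.05. The article does not say whether the Table 2 tests are one- or two-sided, nor does it name the test. I assumed the two-sided two-sample t-test, which is the test named for the primary outcome, and it reproduces the table.

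**Formula.** With d = difference/SD and n per arm, the noncentrality is δ = d·√(n/2). Power is the probability that a noncentral t with 2n − 2 degrees of freedom and noncentrality δ exceeds the two-sided 5% critical value. The normal approximation is Φ(δ − 1.96).

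**Step 1: the primary calculation.** d = 26/44.6 = 0.583. The t-test solution is 47.2 and the normal approximation gives 47, matching the plan. Inflation: 94/(1 − 0.30) = 134.3, stated as 134. In reverse, 134 × 0.70 = 93.8, or 47 per arm.

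**Step 2: reproduce Table 2, then apply the dropout.** Exact t-test powers:

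| Outcome | Difference/SD | d | Stated | No dropout (67 per arm; monitor 34) | 30% dropout (47 per arm; monitor 24) |
|---|---|---|---|---|---|
| Sit-to-stand | 2.0/2.5 | 0.800 | 0.99 | 0.996 | 0.970 |
| CAT | 3.0/5.5 | 0.545 | 0.88 | 0.880 | **0.744** |
| CCQ overall | 0.4/1.1 | 0.364 | 0.55 | 0.552 | 0.415 |
| HADS-A, HADS-D | 1.5/2.5 | 0.600 | 0.93 | 0.932 | 0.821 |
| EQ-VAS | 8/16 | 0.500 | 0.82 | 0.819 | **0.669** |
| Steps per day | 1100/2262 | 0.486 | 0.50 | 0.506 | 0.378 |

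The no-dropout column matches the stated figures to within about 0.01. The steps row does not fit 67 per arm (0.798) but does fit 34. So Table 2 allows for the monitor subset, but not for dropout.

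A hand check by normal approximation:

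- CAT at 67: δ = 0.5455·√33.5 = 3.157, power Φ(1.197) = 0.884.
- CAT at 47: δ = 0.5455·√23.5 = 2.644, power Φ(0.684) = 0.753.
- EQ-VAS at 67: δ = 0.5·√33.5 = 2.894, power Φ(0.934) = 0.825.
- EQ-VAS at 47: δ = 0.5·√23.5 = 2.424, power Φ(0.464) = 0.679.

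The conclusion is the same by either method. A one-sided test at 67 per arm would give 0.93 for CAT and 0.89 for EQ-VAS, which does not match Table 2, so sidedness does not explain the gap.

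**Step 3: how much dropout the claim can bear.** For 80% power CAT needs 54 per arm and EQ-VAS needs 64. From 67 per arm that tolerates 1 − 54/67 = 19% dropout for CAT and 1 − 64/67 = 4% for EQ-VAS. The plan assumes 30%.

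**The case against.** The strongest reply is that nothing in Table 2 is miscalculated. The section states its N openly, and on 67 per arm every figure is right. That is true, but the text goes on to say what the chosen sample size can detect, and the plan itself expects only about 94 of the 134 patients to provide the outcome. Stating the N does not make that conclusion correct.

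A second reply is that 0.74 and 0.67 are powers for an unadjusted t-test, whereas the planned analysis is a mixed model with age, gender, BMI, FEV1 and smoking status as covariates. At 47 per arm, 80% power needs d of about 0.584. That would require the residual variance to fall by 1 − (0.5455/0.584)² ≈ 13% for CAT and 1 − (0.5/0.584)² ≈ 27% for EQ-VAS. The article gives no correlations, so whether this is reached is unknown. It also claims no such gain, and the unadjusted test reproduces its table. Likelihood estimation under missing at random deals with bias; it does not restore the information lost with a missing post-programme score.

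Third, dropout might mean leaving the programme rather than missing the test. But Sample size uses it to inflate the number evaluable for a test-based endpoint, so there it must mean a missing outcome.

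Fourth, secondary status need not depend on 80% power, and the article applies the exploratory label only to two named outcomes. This has some force: CAT and EQ-5D are called secondary consistently, and only CCQ and physical activity carry conflicting labels. But the article gives low power as the reason for the exploratory label, and that reason applies equally to CAT and EQ-VAS once the N is corrected.

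**Conclusion.** The concern holds. On the plan's own dropout assumption, the statement that power exceeds 80% is wrong for CAT (0.74 against a stated 0.88) and EQ-VAS (0.67 against 0.82). It remains true for sit-to-stand (0.97) and, narrowly, for HADS (0.82). CCQ falls from 0.55 to about 0.42 and steps per day from 0.50 to 0.38; both were already below the line.

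These figures rest on a two-sided, unadjusted t-test, the SDs and differences in Table 2, and 30% of patients lacking the 10/12-week value of every outcome. The 24 per arm for the monitor applies the same 30% to the 68-patient subset, which the article does not itself do. Separately, the CCQ label contradicts itself within the article whatever N is used. The primary sample size is not affected.

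**What to change.** 1. Recompute Table 2 at 47 evaluable patients per arm (24 for the activity monitor) and state the test, sidedness and dropout used. If the no-dropout figures are kept, show them beside the corrected ones and label them as such.
2. Limit the above-80% statement to sit-to-stand and HADS.
3. Apply the 80% rule in the same way everywhere, so that CAT and EQ-VAS are treated like CCQ and physical activity. Alternatively, drop power as the ground for the label and say so. Either way, CAT, EQ-VAS, CCQ and physical activity should each carry one status across the abstract, Table 1, the power section and the outcome descriptions, settled before the allocation code is broken.

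The cost is a correction to the text and one table. The stated powers become less favourable. No patients, visits or analyses are added.

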### Study groups

#### Warm-up in both groups (CCRe and CORe)

Warm-up has duration of 5 min (in CORe group) and 10 min (in CCRe group). The aim is familiarization of movements, increasing range of motion and stimulation of joints, muscles and cardiorespiratory warm-up in accordance with recommendations from the American College of Sports Medicine [28]. The warm-up protocol is presented in Table 3.

**Table 3 Tab3:** Warm-up protocol – intervention COPD online rehabilitation

Time	Exercises	Intensity	Progression
Warm-up (duration 5 min)	Sitting or standing: -Heel uprisings (uni- or bilateral), - Kneeextension - rear deltoid row - chest press movement - Vertical shoulder press’ (uni- or bilateral). Standing: -Walking on site - side to side walking - leg curl - leg swing - squats	Non-specific intensity Purpose: -increase body temperature - cardiorespiratory warm-up -muscle and tendon tissue warm-up	none

#### Comparison group - conventional COPD rehabilitation programme (CCRe)

Patients in the comparison group will receive the supervised standard COPD Rehabilitation program (CCRe) for patients with severe and very severe (stage III-IV) COPD, which follows the Danish Health Authority’s National Clinical Guideline and the Regional Guidelines [6, 29, 30]. The guidelines allow for minor variations in the duration of the program (from 10 to12 weeks) but not in the content of the program [6, 29, 30]. The rehabilitation program contains exercise and patient education. Exercise sessions last 60 min twice weekly and will be supervised by skilled physiotherapists with at least 2 years of experience with COPD rehabilitation. The content of the physical exercises is presented in Table 4. Patient education sessions of 60–90 min will take place once weekly following the exercise session. The total number of patient education sessions will vary from 10 to 12 lessons (including follow-up sessions). Topics covered in the education program are presented in Table 5.

**Table 4 Tab4:** Exercise content comparison group - conventional COPD rehabilitation

Exercise type	Exercises	Intensity	Progression
Warm-up (duration 5-10 min)	Sitting or standing: -Heel uprisings (uni- or bilateral), - Kneeextension - rear deltoid row - chest press movement - Vertical shoulder press’ (uni- or bilateral). Standing: -Walking various - leg curl - leg swing - squats	Non-specific intensity Purpose: -increase body temperature - cardiorespiratory warm-up -muscle and tendon tissue Warm-up	none
Endurance training (duration 20-30 min)	-Walking or -Cycle or - Treadmill or - Circuit training or - Activity games	Borg CR-10 dyspnea 4–7 Exercises performed in intervals or continuous	Every 2nd to 4th week load adjustment individualized
Resistance training Duration 20-30 min)	Machine: -leg press -knee extension Pull down and/or chestpres (vertical) Other equipment for strength circuit training elastic band Dumbbells Weight cuff	40–80% of 1RM corresponding from 8 to 25 repetitions 2-3sets	Every 2nd to 4th week load adjustment individualized (repetition counting by supervisor)
Cool-down (duration5-10 min)	Breathing exercises Pursed lip breathe Relaxation exercises Yoga exercises	Non-specific intensity	Non-specific

Responsible health profession: Physiotherapist

Monitoring of intensity may vary, but it is expected that hospitals use either objective (pulse or Watt monitoring) or subjective (CR Borg scale for dyspnea) measurements for intensity monitoring

Resistance training will be evaluated for progression by counting their maximal repetition and estimate a new optional weight/resistance within 8–25 repetitions

Workout logs from every training session are recommended registered by the authorization law

**Table 5 Tab5:** Patients educations topics control group – conventional COPD rehabilitation

Topics/themes	Communication/ learning form
• COPD and the treatment • The importance of smoking cessation • The importance of daily activity and exercise • The importance of nutrition • Medication and use of devices and inhalation technics • Early signs of exacerbation and action plan • Use of nebulizer apparatus and oxygen apparatus. Individually smoking cessation and dietician will be optional for the individual COPD patient if assessed relevant.	Topics are promoted as a combination of: • Information • Dialogue • Reflection exercises • Practical exercises • Focusing on increasing the individual’s self-competence • Networking and exchange of experience.

Responsible health profession: Respiratory nurse

#### Intervention group - COPD online rehabilitation programme (CORe)

Patients in the intervention group will receive the supervised COPD Online Rehabilitation Program (CORe), which is an intervention that has never been systematically offered in Denmark. The CORe intervention is supervised by skilled physiotherapists and respiratory nurses with at least 2 years of experience with COPD rehabilitation, and delivered via a web-cam at Bispebjerg Hospital to a group of 4–8 patients who exercise at home and communicate via a computer. Each session is 60 min, i.e. 35 min of exercise and 25 min of patient education, three times per week for the duration of 10 weeks. The exercises used in CORe exercise program were identified and selected amongst exercises used in previous exercise intervention studies on patients with severe or very COPD and involves larger muscle groups with 50/50% exercises for upper and lower extremities, respectively [4, 5, 31–36]. Volume, intensity and content specified in the training protocol is in accordance with both national and international exercise recommendations [4–6, 29, 30, 37, 38]. The exercises (Tables 6 and 7) are executed in four sets to achieve peripheral muscle fatigue and secondary dyspnea/breathlessness. Each set is carried out in a predefined period of 20 to 40 s with a maximum number of repetitions performed, i.e. 8 to 25 repetitions depending on the patients exercise capacity and motivation [28, 39], but with the aim of 12 to 20 repetitions. The pause is predefined from 40 to 20 s (Table 6). The exercise velocity is based on recommendations applying to high-repetitive exercises (> 15 repetitions) [28], i.e. moderate to high speed equaling 1–2 s for both the concentric and the eccentric movements. The exercise load is body weight supplemented by external weight using dumbbells (1 to 10 kg). The intensity is estimated to be equivalent to 40–80% of one repetition maximum (8–25 repetitions), and exercises are performed as high repetitive time-based muscle endurance training at least 80% of the exercise time corresponding to a weekly volume of 90 min (30 min × 3 sessions). In practice the training intensity is determined by using the self-rated Borg CR-10 scale (score range 0–10), and the aim is to achieve a training intensity corresponding to score 4–7 (moderate to very strong shortness of breath during the exercises).

**Table 6 Tab6:** Exercise protocol intervention group COPD online rehabilitation (Chronological order)

Exercise#	Exercise name	Extremities	Uni/bilateral execution	Bodyposition	Time/volume	Exercise load
1	Sit-to-stand	Lower extremities	Bilateral	Sitting and standing	Active: 80-160 s. Rest:160-80s. Total: 240 s.	Bodyweight and dumbbells
2	Biceps curl -shoulder press	Upper extremities	Bilateral	Standing	Active: 80-160 s. Rest:160-80s. Total: 240 s.	Dumbbells
3	Step-up	Lower extremities	Bilateral	Standing	Active: 80-160 s. Rest:160-80s. Total: 240 s.	Bodyweight, dumbbells and stepbox
4	Bent Over Rowing	Upper extremities	Unilateral	Standing Upper body slightly forward bended	Active: 80-160 s. Rest:160-80s. Total: 240 s.	Dumbbells
5	Static-dynamic Squat	Lower extremities	Bilateral	Standing	Active: 80-160 s. Rest:160-80s. Total: 240 s.	Bodyweight and dumbbells
6	Front Raise Dumbbells	Upper extremities	Bilateral	Standing	Active: 80-160 s. Rest:160-80s. Total: 240 s.	Dumbbells

**Table 7 Tab7:** Progression model - intervention group COPD online rehabilitation (Chronological order)

Phase	Week number	Working volume in seconds	Rest volume in seconds	Number of sets for each exercise
Familiarization	1–2	20	40	4
Progression 1	3–6	30	30	4
Progression 2	7–10	40	20	4

The first 2 weeks serve as a familiarization phase with the purpose to adapt to exercising, adjusting and optimizing load and to avoid musculoskeletal overload injuries. Thus, exercises for the lower extremities (Table 6: exercise # 1, 3, 5) are carried out without dumbbells at the first session. If a patient can perform three consecutive sets without resting during the active period external load is added at the following training session. The external load increase ranges from 2 to 4 k (total weight for two dumbbells) when progression adjustments are made. Exercises for the upper extremities (Table 6: exercise # 2, 4, 6) are carried out with the smallest weights (1 kg / pcs.) at the first exercise session. If a patient can perform three consecutive sets without resting during the active period external load is added at the following training session. The external load increase ranges from 2 to 4 k (total weight for two dumbbells) when progression adjustments are made. Progressions are assessed individually from session to session [31–34]. In addition the patients are asked to count their repetitions in each set every 6th sessions, and if the number of repetitions exceeds 25 the external load is increased at the next training session.

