#### Analysis of primary and secondary outcome

Difference between intervention groups in primary and secondary outcomes at 10/12 week follow-up are analyzed by mixed effect models. Models will include treatment, age, gender, BMI, FEV1 and smoking status, and random effect assessor, hospital allocation and subject. Normal distribution of the model residuals is evaluated by QQ-plots, transformation of outcome may be used if distribution of residuals are not normal. All models will be fitted as listed above, in the event that convergence is not possible or other fitting issue the model structure will be reduced and reasoning for changes will be mentioned.

If all missing data is missing at random, maximum likelihood estimation in the mixed effect models can be done under assumptions of ignorability to account for missing data.

Secondary outcomes will also be analyzed mixed effect model with the same fixed and random effects as the primary outcome.

No interim analysis will be made. Statistical analyses will be carried out using R 3.2.2 (R Foundation for Statistical Computing, Vienna, Austria). *P*-values of less than 0.05 are considered statistically significant.

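### Training-group clustering in the CORe arm is allowed for neither in the sample size nor among the named random effects; if the within-group correlation is above zero, the stated 80% power and 5% error rate do not quite hold

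*Protocol article*

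**What the plan says.** Under the heading for the intervention group, CORe is "delivered via a web-cam at Bispebjerg Hospital to a group of 4–8 patients who exercise at home". Sessions run three times weekly for 10 weeks. Table 7 changes work and rest times by week number, and Table 8 sets a weekly curriculum from introductions in week 1 to the group's own needs in week 10. Patients come from eight hospitals and are randomized individually, 1:1 within each recruiting hospital. The comparison programme (CCRe) is also given in groups, at the local hospital; its group size is not stated.

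The Sample size section starts "Based on a two-sample independent t-test" and concludes, for a difference of 26 m and a standard deviation of 44.6 m: "power of 80% and significance level of 0.05 47 patients will be needed in each group, 94 in total". It then adds: "A dropout rate of 30% is assumed, resulting in 134 patients being included in the final study population". No group size, ICC or design effect enters.

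The primary and secondary outcomes are analysed by mixed models with "random effect assessor, hospital allocation and subject". The same random effects serve every secondary outcome.

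**The concern.** Patients who train together for 10 weeks share sessions, peers and possibly supervisors. The protocol expects CORe to win through better compliance and adherence, which is the kind of behaviour a group may influence. Outcomes in one group may therefore be correlated.

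None of the named random effects represents that correlation. As named, the hospital effect is common to both arms of a recruiting hospital, whereas a training-group effect exists within one arm and does not cancel in the comparison. Even if a CORe group held patients from a single hospital, the term would not separate successive groups. Assessors test at five locations and do not correspond to training groups.

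An unmodelled positive correlation makes the standard error too small. The error goes one way: towards a false claim of superiority, on the primary and all secondary outcomes. Power for a valid analysis is also lower than stated.

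**Working it through.** **Inputs from the article.** Difference 26 m, SD 44.6 m, significance level 0.05 (taken as two-sided), power 80%, 47 per arm, 30% dropout, 134 randomized (67 per arm), CORe groups of 4 to 8.

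**Assumed.** ICC 0.02 to 0.05; the total SD stays at 44.6 m; clustering in CORe only unless stated.

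**1. The stated figure reproduces.** The normal formula gives 2 × (1.960 + 0.842)² × 44.6² / 26² = 46.2 per arm. The exact t-test gives 47.2, so 47 is right to rounding, and power at 47 per arm is 79.9%. For dropout, 94 / 0.7 = 134.3. The arithmetic is sound under independence.

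**2. Group size after dropout.** The 47 per arm are patients analysed after 30% loss, so group size should be on the same footing: 4 × 0.7 = 2.8 and 8 × 0.7 = 5.6 analysed patients per group.

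**3. Formulas.** With m analysed patients per group, the CORe design effect is DE = 1 + (m − 1) × ICC. With equal arms, the variance of the treatment effect is multiplied by A = (1 + DE) / 2. Power is that of a t-test with 47 / A patients per arm. The type I error of a test that ignores clustering is 2 × [1 − Φ(1.96 / √A)].

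| m | ICC | DE | A | Power | Type I error if ignored |
|---|---|---|---|---|---|
| 2.8 | 0.02 | 1.036 | 1.018 | 79.1% | 5.2% |
| 5.6 | 0.02 | 1.092 | 1.046 | 78.0% | 5.5% |
| 2.8 | 0.05 | 1.090 | 1.045 | 78.1% | 5.5% |
| 5.6 | 0.05 | 1.230 | 1.115 | 75.3% | 6.3% |
| 8 (no loss in groups) | 0.05 | 1.350 | 1.175 | 73.1% | 7.1% |

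For the fourth row, the standard error rises from 44.6 × √(2/47) = 9.20 m to 9.20 × √1.115 = 9.71 m. For the last row, a simulation of unadjusted t-tests gave a type I error of 7.0%.

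**4. If CCRe groups cluster equally and the hospital term absorbs none of it**, then A = DE. At ICC 0.05 and m = 2.8 to 5.6, A is 1.09 to 1.23, power 76.3% to 71.1%, and the type I error roughly 6% to 7.7%.

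**5. Do CORe groups mix hospitals?** The article does not say. If recruitment is even, 67 / 8 ≈ 8.4 CORe patients per hospital over about 21.5 months (18 March 2016 to 31 December 2017) is about 0.4 per month. One hospital would need about 10 months to fill even a group of 4, so mixing is likely.

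**6. Number of CORe groups.** 67 / 8 ≈ 8 to 67 / 4 ≈ 17.

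**The case against.** The strongest reply is that the harm is conditional. The documents give no ICC, and some features point to a low one: load is adjusted individually, intensity is self-rated, the exercise protocol is standardized, and if a single team runs every CORe group its influence is common to the arm. At an ICC of 0.01, with 2.8 to 5.6 analysed per group, power is still about 79%. Dropout below 30% would also help: with all 67 per arm analysed, power under independence is 91.8%. The type I figures describe a test that ignores all clustering, whereas the planned model has hospital and assessor effects and covariates.

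Most of this stands, and it limits the size of the point. It does not remove it. The independent t-test and the random effects are both named in the text, so this is not a detail merely left to a fuller document. More analysed patients would restore power, but would not make an unclustered standard error valid.

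A reader might go further and conclude that the standard errors are too small as a matter of fact, that true power is 73% to 78%, or that CORe uses fixed groups drawn across hospitals. The documents do not support this. The first two need an ICC that is not given, and power as low as 73% at ICC 0.05 pairs full groups of 8 with an analysed sample that has already lost 30%. Closed cohorts and mixing of hospitals are inferences from the weekly curriculum, central delivery and the recruitment rate; neither is stated.

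**Conclusion.** The point holds in conditional form. The plan describes group delivery, then sizes the trial and names its model as though training groups did not exist. For any positive within-group correlation, the standard error is too small and power is below the stated figure. On the assumptions in the table, the cost is about 1 to 5 percentage points of power, and 0.2 to 1.3 points of type I error if clustering is ignored. It would be larger if groups stay full or if CCRe groups also cluster beyond what the hospital term absorbs. The 47 per arm and 134 in total are not miscalculated. This is a worthwhile correction of modest size, not a flaw that undermines the design.

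**What to change.** Record each patient's training-group identifier; the exercise log as described does not list one. Before unblinding, specify a training-group random effect in the CORe arm (a partially nested model), and use hospital-cohort for CCRe where several trial patients train together. Neutral codes in both arms would help to keep the statistician blinded. State that the 80% power assumes no group clustering, and give power over a range of assumed ICCs rather than one replacement figure.

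The article already allows the model to be reduced if it does not converge. That rule should drop assessor before training group.

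The cost is one extra data item, one model term, slightly wider intervals and a less favourable stated power. With only about 8 to 17 CORe groups the variance component will be imprecisely estimated, which is why the order of dropping terms should be fixed in advance.
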